**Figure 3. F3:**
[figure not shown]
The theory of planned behavior (TPB) applied to the FiberMore intervention.

The primary strategy involves the use of progressively challenging yet attainable goal-setting using a simple algorithm based on our previous work [20], which has been shown to enhance control beliefs and self-efficacy. Specifically, the chatbot suggests a new fiber intake goal each week, tailored to the participant’s performance in the previous week based on the number of days the goal was met (see Table 1).

Participants can monitor their daily progress toward their fiber goal through a real-time update graph displayed on the app’s home screen. Additionally, participants are able to view weekly goal achievement progress through this graph, supporting mastery experience and reinforcing a sense of achievement.

To further support PBC, participants receive personalized feedback on the fiber content and fiber-to-energy ratio of their meals. These feedback messages aim to increase participants’ awareness and perceived ability to make appropriate dietary choices, thereby reinforcing control beliefs. A third mechanism enhances PBC via daily self-assessment of coping strategy implementation and weekly setting of new barriers and corresponding coping strategies. Setting coping strategies can enhance the optimistic beliefs about one’s capability to cope with barriers that arise, leading to improved self-efficacy and a stronger sense of PBC when facing obstacles [43]. Another mechanism involves the “Learn More” chatbot, which provides useful information and tips on increasing fiber intake, aiming to enhance users’ confidence and perceived control over increasing their dietary fiber.

Beyond influencing PBC, the FiberMore intervention may also impact actual behavioral control (ABC). ABC measures the extent to which a person has the skills, resources, and other prerequisites needed to perform the behavior [44]. FiberMore’s provision of meal fiber values, daily fiber totals, and “Learn more” education on fiber may improve ABC by giving actionable information. To the extent that the solution offered to the barrier is new to the participant and effective, the barrier/solution process may increase ABC.

FiberMore also seeks to influence behavioral beliefs by shaping a positive emotional attitude toward the behavior, which in turn may increase users’ motivation and intention to perform the behavior [44]. This is implemented through a weekly “checking in” chatbot that encourages users to reflect on what aspects of increasing fiber intake have been enjoyable or challenging. In response to user input, the chatbot delivers empathetic messages, validates users’ experiences, and offers positive reinforcement to enhance emotional attitude toward increasing fiber intake.

We hypothesize that the FiberMore intervention will lead to improvements in participants’ attitude and PBC toward increasing dietary fiber intake. These changes are expected to enhance their intention to consume more fiber, which in turn will result in an increase in fiber intake (see Figure 3).

We will measure the impact of the FiberMore intervention on TPB outcomes via a questionnaire of 20 direct TPB belief measures of intention (questions 1‐5), attitude (questions 6‐11), subjective norms (questions 12‐14), and PBC (questions 15‐20) regarding eating more fiber-rich foods than usual. The scoring of each scale for the belief measures is 7-point from 1 to 7. This TPB questionnaire was developed with reference to a previously validated instrument targeting high-fiber dietary intake [45], and was guided by the TPB questionnaire development manual by Francis et al [46]. It has been previously tested among the T2D population in Japan and content-validated by diabetes specialists and researchers experienced in health behavior change research [35].

### Study Procedures and Participant Timeline

#### Preliminary Study Enrollment

The physicians at each research institution will conduct screening procedures to T2D patients who visited the outpatient clinic according to the inclusion and exclusion criteria of this study. A clinical research coordinator (CRC) will approach eligible patients to provide detailed information about this study and to obtain the patient’s written consent to participate in this study. Once consent to participate in this study is obtained, the CRC will assist study participants to download MealLog onto participants’ mobile phones and explain to study participants how to log meals through the app (see Table 2).

**Table 2. T2:** Details of MealLog features.

Meal logging options in MealLog	Description
Snap a meal (or upload from phone gallery)	Study participants log a meal by taking a photo of the meal via the MealLog app. The meal photo is uploaded to the AI^a^ server and analyzed for its fiber, energy, carbohydrates, protein, fat, and salt amounts. No feedback on the meal is provided to the user via the app.
Chat a meal	Study participants describe a meal with the “Chat a meal” chatbot (EiYouBot) on the MealLog app to log the meal. Based on the description, the meal is analyzed by the AI server for its fiber, energy, carbohydrates, protein, fat, and salt amounts. No feedback on the meal is provided to the user via the app.
Snap a meal (or upload from phone gallery) followed by Chat a meal	Study participants first log a meal by taking a photo via the MealLog app. The meal photo is uploaded to the AI server and analyzed for its fiber, energy, carbohydrates, protein, fat, and salt amounts. No feedback on the meal is provided to the user via the app. Study participants then describe additional details about the meal with EiYouBot. Nutrient values are updated according to their added details.

a AI: artificial intelligence.

#### Run-in Period

During the run-in period, preliminarily enrolled study participants will use MealLog to log their meals so that the researchers can assess their average baseline fiber intake. A research co-investigator will contact the study participants via SMS text messages if participants do not log any meals or if only 1 meal is logged for 3 days consecutively since the start of the run-in period.

To be eligible for official study enrollment, study participants need to log at least 2 eating occasions (either main meals or snacks) in app per day for at least 7 days during the nominal 14-day run-in period and have an average baseline fiber intake of less than 20 g per day (after excluding days with 0 or 1 logged meal per day).

On the first 3 days of the run-in, at 11 AM, preliminarily enrolled study participants will receive an SMS containing a survey link for the TPB questionnaire (via Jotform). On day 1 of the run-in, study participants will receive a TPB questionnaire on increasing fiber intake. On day 2 of the run-in, they will receive a TPB questionnaire on reducing salt intake. On day 3 of the run-in, they will receive a TPB questionnaire on reducing saturated fat intake. Study participants are required to complete these surveys at home or at any convenient location with an internet connection. If the questionnaire submissions are not received by the 3rd day of the week, another SMS text message will be sent on the 4th day as a reminder to complete the missing questionnaire.

After completion of the run-in period, study participants will be contacted by the research office about their official study enrollment status.

#### Official Study Enrollment and Randomization

Randomization will be conducted using a dynamic allocation method based on minimization, with an allocation ratio of 1:1. The allocation adjustment factors will include the baseline dietary fiber intake during run-in (under 10 g, 10 g and above), sex (male and female), and HbA_1c_ level on the date of consent (less than 8.5% and 8.5% or higher). Random allocation will be performed online using the INDICE cloud system provided by the University Hospital Medical Information Network (UMIN). After randomization, a CRC will explain the details of the intervention according to the study participants’ allocated group (intervention or control). Participants are blind to their group.

#### The Intervention Condition

A CRC will assist study participants assigned to the intervention group with downloading FiberMore onto their smartphones and input the initial fiber goal of the study participants to the backend system (refer to Table 2 for determination of the initial goal). The CRC will also assist the study participants to identify 1 barrier on increasing fiber intake and its corresponding solution via the “Barrier and Solution” chatbot within FiberMore. The CRC will also provide guidance and demonstration on using the intervention features of FiberMore.

The CRC will give study participants a handout on the benefits of increasing fiber intake as well as general tips and examples about eating more fiber. As some study participants depend on their family for meal preparation, the CRC will encourage the study participant to share the educational handout with their family members and communicate the weekly fiber goal as well as the feedback obtained from FiberMore with their family or person preparing their meals.

On the first three days during week 10, at 11 AM, study participants will receive an SMS text message containing a survey link for a TPB questionnaire (via Jotform). On day 1 of week 10, study participants will receive a TPB questionnaire about increasing fiber intake. On day 2, they will receive a TPB questionnaire about reducing salt intake. On day 3, they will receive a TPB questionnaire about reducing saturated fat intake. Study participants are required to complete these surveys at home or any convenient location with an internet connection.

#### The Control Condition

After randomization, the control group will receive an educational handout on salt intake reduction as well as a paper diary to record their efforts in reducing salt intake. They are encouraged to record any small effort to reduce salt intake in the diary on a daily basis. They will also receive web-based educational information via SMS text message once during week 4 and once during week 8 (see Figure 4). On the last day of week 10, the control group will receive SMS text message reminders from the research office to use MealLog to log their meals for 14 days during week 11 and week 12 (see Figure 5).

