A recent study based on the TPB revealed that while T2D patients in Japan are aware of the benefits of consuming more dietary fiber, the 2 main barriers they faced are a lack of knowledge about high-fiber foods and difficulty in estimating fiber content in meals [35]. Attitude and perceived behavioral control (PBC) were found to predict intention to increase 50% more dietary fiber than patients’ usual intake [35]. This highlights the need for an intervention that provides real-time feedback on dietary fiber intake for each meal, along with educational information to support fiber consumption. Nevertheless, evidence has suggested that manual food logging in dietary apps can be burdensome, leading to reduced user engagement in diet self-monitoring over time [19,26]. Image-based dietary assessment, facilitated by artificial intelligence (AI), could address this issue by streamlining the process of food logging, thus reducing user burden [36]. This method has also been shown to potentially exceed the accuracy of human estimations of nutrient content based on digital food images [37], particularly in the assessment of dietary fiber [38,39]. Furthermore, AI is capable of offering personalized nutritional advice and meal plans [40]. Leveraging this strength of AI allows us to build a diet intervention in line with the JDS’s recommendation to honor patients’ personal diet preferences while administering medical nutrition therapy [15].

Based on the above research findings, we developed FiberMore, an AI-powered diet intervention app that uses TPB to help T2D patients increase their dietary fiber intake by enhancing their PBC and attitude toward fiber consumption. To our knowledge, this is the first study to use an AI-based bot to deliver fiber-focused feedback based on the assessment of meal photos. While many nutrition apps focus on improving general health care concerns, apps that focus on specific chronic diseases and the nutrition involved in the disease state are limited [26]. Currently, dietary interventions specifically targeting improving dietary fiber intake among T2D patients have not been developed in Japan, thus highlighting the novelty and importance of this behavior change intervention. The purpose of this single-blind, randomized controlled trial is to examine the preliminary efficacy of an AI-assisted, app-based mHealth intervention to promote dietary fiber intake among T2D patients, leading to improved blood glucose control.

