### Sample Size Consideration

The primary outcome is the difference between the intervention group and the control group in the change in mean daily dietary fiber intake from the time of study enrollment to the end of the intervention period. We desired to detect a between-group difference in the mean change of 7 g of dietary fiber, drawing from a meta-analysis, which demonstrated a 9% risk reduction of cardiovascular disease events for 7 g increase in daily dietary fiber intake [47]. A previous RCT reported a 7.9 g/day increase in fiber intake at 3 months in the high-fiber group, supporting the use of a 7 g/day between-group difference as a realistic and meaningful target [33].

Based on the findings from a previous nutritional intervention research in Japan [48], we assumed a common SD of 9.85 g for the difference in dietary fiber change across both groups. Using a 2-sided significance level of 5% and a power of 80%, the required sample size calculated based on an independent *t* test is 33 participants per group. A study conducted in a similar population, which followed a similar study structure with a 2-week run-in phase, a 12-week intervention phase, and a subsequent 12-week observation phase by our research team showed minimal to no dropout throughout the study duration [49]. Nevertheless, as a conservative estimate to account for potential attrition, we aimed to enroll a minimum of 70 participants. The 2-week run-in phase also ensures that we enroll the participants who are able to use the app as instructed, thus minimizing drop-out risk.

Based on the findings from previous studies implemented in our research lab, we estimate a 10% dropout rate between preliminary and official study enrollment. Therefore, the target recruitment number for the preliminary study enrollment has been set at 77 participants.

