### Primary Outcome Analysis

We will perform analysis of covariance on the change in dietary fiber intake from the time of run-in to the end of the intervention period, with dietary fiber intake from the time of run-in as the covariate. The change in dietary fiber from the time of run-in and at the end of the intervention period will be calculated as ([average dietary fiber over week 11 and 12]-[average baseline dietary fiber during the run-in]). The estimated mean change in each group and its 2-sided 95% CI will be calculated. Additionally, the estimated difference between groups and its 2-sided 95% CI will be calculated.

To ensure reliable estimates of fiber intake, days with only 0 or 1 logged meal will be excluded from the analysis.

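### Intervention-arm primary data are collected only through the treatment app, and the explicit weeks 11-12 logging prompt is described for controls only, so missing data may differ by arm and the fiber effect may be overstated

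*Protocol article*

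**What the plan says.** All references are to the protocol article.

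- **Outcome source.** Primary Outcome Analysis defines the outcome as average fiber in weeks 11 and 12 minus the run-in average, and states that "days with only 0 or 1 logged meal will be excluded from the analysis". Table 3 shows where the values come from: FiberMore throughout the 12 weeks in the intervention arm, and MealLog in weeks 11 and 12 only in the control arm. The E3 visit collects laboratory values, vital signs and questionnaires, but no fiber measure.
- **Prompt in the control arm.** The Control Condition: "On the last day of week 10, the control group will receive SMS text message reminders from the research office to use MealLog", for 14 days.
- **Prompt in the intervention arm.** The Intervention Condition describes the week 10 survey messages in detail but has no counterpart to that logging message. Table 1 lists weekly in-app notifications for goals, barriers and emotional attitude. The Discussion mentions SMS and LINE reminders about visits and intervention schedules for participants in general.
- **Chasing non-loggers.** Run-in Period provides for staff contact "if participants do not log any meals or if only 1 meal is logged for 3 days consecutively since the start of the run-in period". No similar rule is described for weeks 11 and 12.
- **Analysis set.** Statistical Analysis Plan admits to the full analysis set anyone with at least one post-randomization primary or secondary outcome, analyzed as assigned.

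**The concern.** In the intervention arm, adherence to treatment and supply of the primary outcome are the same act. A person who gives up FiberMore in week 6 but attends E3 contributes HbA1c and the other secondary outcomes but no fiber value. In the control arm, giving up the salt diary has no such consequence, because MealLog is a separate tool that is restarted on request.

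People who stop a fiber app may well be those who gained least from it. If so, the comparison drifts from everyone randomized towards persisting FiberMore users against controls who answered a logging request. That would push the primary estimate upward under an analysis described as intention to treat. An analysis plan can say how to handle such gaps, but it cannot recover fiber data that were never collected.

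**Working it through.** **1. The plan's own figure.** The inputs, from Sample Size Consideration, are a 7 g difference ("We desired to detect a between-group difference in the mean change of 7 g of dietary fiber"), an SD of 9.85 g ("we assumed a common SD of 9.85 g for the difference in dietary fiber change across both groups"), two-sided 5% and 80% power.

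- Normal approximation: n = 2 × (1.960 + 0.842)² × 9.85² / 7² = 31.1, so 32 per group.
- Exact t test: 32.07, so 33 per group, as stated ("test is 33 participants per group"). Power at 33 is 81.1%.
- Raising 66 to 70 allows for 1 − 66/70 = 5.7% loss. With the 72 randomized split 1:1, 36 per arm with complete data give 84.5% power.

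The sample size is sound. It bears on precision, however, and extra participants do not remove a bias.

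**2. Who can have a primary value.** Take an intervention participant who has stopped logging in FiberMore by week 11 but stays in the study. All 14 days have no logged meal, so all are excluded and no change can be computed. HbA1c at E3 keeps the person in the full analysis set. MealLog was installed for everyone at preliminary enrollment, but no section describes its use in this arm after the run-in.

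**3. Illustration by mixture.** Let p be the share of the intervention arm without data. The value of p is an assumption, since the documents give none. Suppose that control data are complete, that stoppers change by the control mean, and that remaining users gain D = 7 g over control.

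- Reported effect = D. All-randomized effect = (1 − p) × D + p × 0.
- p = 10%: 0.9 × 7 = 6.3 g. Overstatement 7/6.3 − 1 = 11%.
- p = 20%: 0.8 × 7 = 5.6 g. Overstatement 25%.
- p = 30%: 0.7 × 7 = 4.9 g. Overstatement 43%.

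**4. A second mechanism.** Let the tendency to keep logging correlate with a person's own fiber change at ρ (assumed), with selection in the intervention arm only. Then bias = ρ × 9.85 × φ(z) / (1 − p), where z is the standard normal quantile for p. For p = 20%, φ(z) = 0.280, and 0.280/0.8 × 9.85 = 3.45 g, which is then multiplied by ρ. The type I error comes from 20,000 simulated trials with 36 per arm and an unadjusted t test.

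| p | bias, ρ = 0.3 | bias, ρ = 0.5 | two-sided type I error |
|---|---|---|---|
| 10% | 0.6 g | 1.0 g | 5.5% to 7.1% |
| 20% | 1.0 g | 1.7 g | 6.6% to 10.7% |
| 30% | 1.5 g | 2.5 g | 8.8% to 15.2% |

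The bias is zero if ρ = 0, or if loss and selection are the same in both arms. It changes sign if selective loss is heavier among controls.

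**The case against.** Several stronger readings are tempting, and the documents do not support them.

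- **That the protocol itself predicts fading engagement.** The Introduction does speak of burden "leading to reduced user engagement in diet self-monitoring over time", but about manual food logging, and goes on to present AI image logging as a possible remedy. The Discussion adds that logging by chat lowers the chance of missed records. The per-protocol rule on sparse logging shows only that non-logging is foreseen as possible.
- **That the intervention arm is never prompted.** It receives weekly in-app notifications, and the SMS and LINE reminders are not limited to one arm. What stands is narrower: neither is described as a request to log for the outcome window, and in-app notices may miss someone who has left the app. The control message also has a plain purpose, since controls must restart a dormant task.
- **That non-responders do drop out and the effect is inflated.** No stopping rate is given, and nothing links stopping to response. Controls resume logging after 10 weeks without it and may fail to do so selectively. The Discussion itself notes that controls may comply less if they think their treatment inactive.

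Other points limit the size. Participants had to be willing to log and had to log adequately on at least 7 run-in days. No minimum number of valid days is stated, so on the text even one adequately logged day yields an outcome and only near-total stoppers are lost. The team's similar earlier study had little dropout, but that refers to leaving the study, not to ceasing to log.

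The missing-data method may well be in the full protocol or analysis plan and is not criticized here. The Discussion's argument that one assessment method serves both arms answers AI measurement error, not the question of who supplies data.

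**Conclusion.** The point holds as a design risk. As described, primary outcome collection in the intervention arm depends on continued use of the treatment, and the explicit logging prompt before the outcome window goes to the other arm only. Missingness may therefore differ by arm and be informative, and the fiber effect may be overstated. A reader might infer that it will be overstated by 11% to 43%. That range rests on assumed stopping of 10% to 30%, stoppers changing by the control mean, complete control data and remaining users gaining 7 g over control. The selection model gives 0.6 to 2.5 g on its own assumptions. Neither is a forecast, and selective non-logging by controls could cancel or reverse the bias. The case for acting is that the safeguard is cheap and protects the primary comparison.

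**What to change.** For participants not yet past week 12:

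1. Send both arms the same message at the end of week 10, asking for 14 days of meal logging.
2. Apply the same non-logging contact to both arms in weeks 11 and 12, for example the run-in rule.
3. Let intervention participants who have stopped FiberMore record those weeks in MealLog, and analyze them in their assigned arm.

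For all participants:

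4. Report by arm how many have weeks 11-12 data and how many valid days they supply.
5. Unless the analysis plan already holds it, add a sensitivity analysis that gives intervention participants without weeks 11-12 data the control-arm mean change. Multiple imputation around that mean would avoid an artificially small standard error.

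The cost is one further automated message, staff time for contacts, renewed use of an app already installed for the run-in, and one extra analysis. Recruitment ran from February to September 2025 and the intervention period is expected to end in December 2025. Steps 1 to 3 would therefore change collection mid-trial, could not apply uniformly and would miss early enrollees. The date of the change should be recorded. The reported effect may also turn out smaller.
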